### Objective measures

#### Actigraphic sleep continuity measures

To obtain objective measures of sleep continuity, for example, sleep onset latency, total sleep time, wakefulness after sleep onset and sleep efficiency (ie, total sleep time divided by time in bed), an actigraphic device worn on the wrist (MotionWatch 8, CamNtech, Manor Farm, Cambridgeshire, UK) will be used for several weeks throughout the study (see figure 1). Actigraphic devices record movements (and light) that can be used to estimate sleep parameters.^49 50^ Comparison to the gold standard for assessment of sleep, polysomnography, shows that actigraphy in general produces similar estimates of sleep duration (total sleep time) and sleep efficiency, although there may be an overestimation of these variables through actigraphic assessment in populations with poor sleep and low activity levels.^51^ Nevertheless, actigraphy provides the opportunity to assess sleep over extended periods in the person’s natural sleep environment, which is a great advantage compared with polysomnography, especially considering that insomnia symptoms are often variable over time.

#### Quantitative sensory testing measures of pain

To obtain assessments of pain thresholds and dynamic measures of pain (eg, central sensitisation), a comprehensive quantitative sensory testing (QST) protocol will be applied. All testing will be performed in a quiet, air-conditioned (20–24°C) room. Testing will be conducted by one out of two experienced research nurses who have obtained extensive training in the methods used. Throughout the QST, participants will be asked to keep their eyes closed to enable complete focus on the evoked sensations. Brief demonstrations of the different procedures will be performed prior to testing. The following procedures will be performed:

Assessment of *fibromyalgia tender points* (according to American College of Rheumatology (ACR) 1990 criteria) through application of pressure (4 kg).Assessment of *pressure pain detection threshold* (PPDT) using a digital algometer (SBMEDIC Electronics, Solna, Sweden) with a 1 cm^2^ probe area applied to the skin at a constant rate of 30 kPa/second. The participant will be instructed to indicate (through pushing a button) when the stimulus ‘first feels painful’. Testing will be performed with the participant in a supine position. In the case of participants undergoing THA, four locations will be examined: (1) a proximal, volar area on the forearm (bilateral) and (2) the area overlying the major trochanter (bilateral). For those undergoing TKA, the locations will also include a proximal, volar forearm area, but instead of the major trochanter, an area adjacent (medial and proximal) to the femorotibial junction (ie, just above the ‘fatty pad’) will be examined (bilateral). Two trials with a 30 s interstimulus interval will be completed per area. Subsequently, pressure pain testing will be performed once in each area to ascertain which level of pressure (kPa) is required to elicit pain corresponding to NRS 4/10 (ie, PP4) and NRS 7/10 (ie, PP7), respectively.To examine *temporal summation* (TS), that is, central nervous system augmentation of pain caused by repeated painful stimulation, mechanical stimulation will be applied to three areas (THA: area overlying the major trochanter on the affected side, the contralateral area and ‘the triangle’ between the first and second metacarpal bones on the dorsum of the left hand; TKA: knee-area described above, the contralateral area and the same ‘triangle’ on the dorsum of the hand described above). A weighted pinprick stimulator (‘PinPrick’, MRC Systems GmBH, Heidelberg, Germany) calibrated to deliver 256 nM of force will first be applied to the skin in an area which will not be tested subsequently. The participant will be asked to rate how painful the stimulus is on a scale from 0 to 100 (0=no pain, 100=worst pain imaginable); if the participant perceives this stimulation to be painful, the 256 mN stimulator will be used throughout the TS testing, otherwise a 512 mN stimulator will be used. The participant will first rate how painful a single pinprick stimulus is in each of the three testing areas. Thereafter, a train of identical 10 pinprick stimuli, at a frequency of 1 per second (1 Hz), will be administered within an area of 1 cm^2^. The participant will rate the peak pain experienced during the testing sequence, whereafter TS will be calculated as peak pain rating divided by pain rating of single initial stimulus. In case the participant rates the first stimulus as 0 (ie, no pain), a minimum value of 1 will be assigned in order to enable calculation of TS. Assessment of TS will be performed twice in each area, with a 2 min pause between tests. Results from the two sets of testing will be averaged.*Conditioned pain modulation* (CPM), that is, the capacity of endogenous pain inhibitory systems, will be assessed through a QST paradigm comprising an ischaemic pain (tourniquet) conditioning stimulus and a pressure pain test stimulus (as described in detail by Tour *et al*^52^). First, PPDT will be assessed twice in a midpart area of the thigh contralateral to the hip/knee which will undergo surgery (near the crossing of the sartorius and rectus femoris muscles); subjects will also be asked to report pain intensity (NRS 0–100) in the contralateral arm. Then, a tourniquet will be placed on the contralateral arm, and subsequently inflated to constrict blood flow. The subject will then be given a 2 kg weight to perform reverse wrist curls, to elicit ischaemic pain in the left forearm and hand. Once the pain reaches a level corresponding to NRS 50/100, the investigator will repeatedly assess PPDT in the area specified above, at 30 s intervals. Maximally, eight measurements will be conducted prior to the release of the tourniquet. The subject will then be asked to rate the maximum arm pain perceived during the test, as well as pain in the hip/knee after the test. Finally, following 5 min of rest, two PPDT measurements will conclude the CPM testing session.To assess *cold pain tolerance*, a circulating, cold water bath (2°C) will be used (Somedic AB, Hörby, Sweden). Participants will first be asked to report pain intensity in their hip/knee and the contralateral hand. Thereafter, participants will immerse the contralateral hand up to the wrist in the cold water, up to an uninformed 4 min maximum time limit. Participants will be instructed to indicate when the cold first starts feeling painful (cold pain detection threshold), and to keep their hand in the water for as long as possible, until the cold pain becomes intolerable (cold pain tolerance threshold). If the participant is able to keep their hand in the water throughout the full 4 min period, the test will be aborted and the cold pain tolerance threshold assessed as 240 s. Immediately after the test, subjects will be asked about maximum pain in the hand, as well as pain in the hip/knee. Finally, after 5 min of rest, participants will once again be asked to report pain intensity in these locations.

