**Trial registration number:**

NCT06145516.

STRENGTHS AND LIMITATIONS OF THIS STUDYIntervention will be delivered prior to orthopaedic surgery, as a prehabilitation approach, for the treatment of insomnia.Unmeasured confounding will be mitigated by a randomised, outcome-assessor blinded, active comparator design.Intervention efficiency, accessibility and scalability will be maximised by self-guided digital-based delivery methods.Potential mechanisms of action will be informed by multimodal assessments of perioperative sleep and domains related to postoperative recovery.Study generalisability will be challenged by participant enrolment and adherence in the context of major orthopaedic surgery.

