#### Sleep education therapy

When evaluating psychological interventions, it is important to include an active comparator control treatment.^24^ In this trial, we will be using sleep education therapy (SET), administered in digital self-guided form over a 4-week period. Topics of the SET include sleep physiology, sleep disorders, general health and ageing, complementary medical approaches, health factors relating to sleep and sleep hygiene measures. This type of control condition has previously been found adequate in CBT-I trials.^28^ In addition to the digital format, telehealth video consultations with a research nurse will be provided once weekly (up to a maximum of 60 min per session) over the 4 weeks. The two research nurses involved in the study will receive adequate pretrial training related to sleep physiology, sleep hygiene and behavioural changes, to enable effective support of study participants. Identical to the CBT-I intervention, a telehealth SET booster session will be administered 1–2 weeks after surgery. Briefly, the educational information will describe learning objectives and patient activities to promote integration of the material. SET is known to produce modest benefits in insomnia, although not as robust or durable as for CBT-I.

An overview of the key components included in the digital interventions is provided in table 1.

**Table 1 T1:** An overview of the key components included in the digital interventions

Components of sleep education therapy (4 weeks)	Components of CBT-I (FastAsleep) (4 weeks)
Digital tool: notebook.	Sleep registration and sleep window adjustment tool: a simplified sleep diary, logs bedtime, rise time, time awake during the night and subjective sleep quality. Sleep efficiency is calculated automatically for every registered night. After every four registered nights, the patient is invited to adjust their sleep window, that is, maximum of six adjustments.
Education component week 1: myths about sleep. Sleep hygiene education. The types of sleep problems.	Module 1: Psychoeducation regarding sleep and sleep difficulties; sleep hygiene information; rationales for stimulus control and sleep restriction therapy. Introduction of patient narratives.

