Education component week 2: the biology of sleep. Stress and the immune system, in relation to sleep.	Module 2: Short module focusing only on common problems and suggestions for solutions, encouragement to carry on despite possibly increased daytime sleepiness. Follow example patients on their journey towards better sleep.
Education component week 3: medical conditions that can interfere with your sleep. Dreams and nightmares.	Module 3: Short module focusing only on continued problem solving and encouragement to carry on even if improvement has yet to occur. Follow example patients on their journey towards better sleep.
Education component week 4: psychological treatments for sleep problems. Alcohol, benzodiazepines and other sleep aids.	Module 4: Short module focusing only on continued problem solving and encouragement to carry on even if improvement has yet to occur. Follow example patients on their journey towards better sleep.
(No maintenance plan)	Module 5: Maintenance plan and advice on management of possible setbacks and relapses. Follow example patients on their journey towards better sleep.

CBT-I, cognitive behavioural therapy for insomnia.

Significant efforts will be made to retain study participants in the assigned intervention group; measures include text notifications, e-mails and phone calls, as needed. Moreover, the support provided by psychologists/research nurses is designed to maximise retention.

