### Blinding (masking)

To reduce the risk of bias, investigators, outcome assessors and data analysts will be unaware (blind) of the intervention to which the trial participants have been assigned, on intervention assignment and beyond. Participants will be aware that they are assigned to an intervention for the treatment of insomnia. The consent form states that participants will be assigned at random to either CBT-I or SET, and that both interventions are used for treatment of insomnia. The programme content of the alternative treatment will not be revealed. Although there is limited information related to objectives of the trial in the consent form, participants will be blind to most objectives and study hypotheses.

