### Data collection methods and data management

Data will be collected through REDCap, in paper forms (eg, some questionnaires, interviews, QST results) and in digital format (eg, cognitive testing, actigraphic assessment). Data will be transcribed from source documentation directly into a statistical programme (eg, SPSS), or, in the case of results obtained through digital cognitive testing, directly captured and converted into a statistical programme. When data are collected on paper forms, data entry will be performed locally, to enable immediate correction of missing or inaccurate data. Assessors (research nurses) will receive training to promote data quality. Prior to analyses, the lead statistician will verify that the data are in the proper format and within an expected range of values. Additionally, there will be an independent verification of a random subset of data (∼10%) to identify missing or erroneous values. During, and up until 10 years after the trial has been completed, paper forms will be stored securely in binders placed in locked file cabinets at the study site.

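### Outcome-assessor blinding is not secured for nurse-administered testing after randomisation, because the same two research nurses appear both to deliver the control sessions and to test

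*Protocol article*

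**What the plan says.** All references are to the protocol article.

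- **Control arm delivery (Sleep education therapy).** "telehealth video consultations with a research nurse will be provided once weekly" over the 4 weeks. The section continues: "The two research nurses involved in the study will receive adequate pretrial training related to sleep physiology, sleep hygiene and behavioural changes", so that they can support participants. It adds that "a telehealth SET booster session will be administered 1–2 weeks after surgery", without naming who gives it. CBT-I sessions are given by a psychologist.
- **Testing (Quantitative sensory testing measures of pain).** "Testing will be conducted by one out of two experienced research nurses who have obtained extensive training in the methods used".
- **Assessors (Data collection methods and data management).** "Assessors (research nurses) will receive training to promote data quality".
- **Blinding (Blinding (masking)).** "investigators, outcome assessors and data analysts will be unaware (blind) of the intervention to which the trial participants have been assigned", from assignment onwards. No exception is made.
- **Strengths and limitations list.** The trial is described as having a "randomised, outcome-assessor blinded, active comparator design", and this is credited with mitigating unmeasured confounding.
- **Timing (Participant timeline).** Randomisation follows completion of visit 1. Visit 2, after the intervention, repeats nearly all visit 1 procedures. The 6-month visit repeats those of visit 2 and adds testing for chronic postsurgical pain (CPSP).

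**The concern.** A nurse who has held weekly sessions with a participant knows that the participant is in SET, because the other arm is seen by a psychologist. If that nurse then performs the QST, the tester is unblinded for that participant. The tester also gains some information about everyone else, since a participant whom the nurse has not counselled is more likely than not to be in CBT-I.

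QST leaves room for the tester to matter. The nurse gives the instructions, applies the pinprick trains, collects verbal pain ratings and encourages the participant to keep a hand in cold water as long as possible. Temporal summation and conditioned pain modulation are named in the abstract among the secondary outcomes, and the Discussion relies on QST to interpret mechanism. An existing counselling relationship in one arm only could also affect ratings, apart from any expectation the tester holds.

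At stake is whether these secondary results can be reported as assessor-blinded. Blinding lost during conduct cannot be restored in the analysis.

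**Working it through.** The article gives no figure for this point, so the first step is a reading of roles. The arithmetic after it only shows scale.

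**Step 1: who does what.**

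| Role | Staff named | Section |
|---|---|---|
| Weekly SET sessions | Research nurse; two in the study | Sleep education therapy |
| QST | One of two research nurses | Quantitative sensory testing measures of pain |
| Outcome assessor | Research nurses | Data collection methods and data management |
| Weekly CBT-I sessions | Psychologist | Cognitive behavioural therapy for insomnia |

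The first section refers to the two research nurses of the study as a complete set. The next two draw testers and assessors from research nurses. The natural reading is that they are the same two people. This is a strong inference; the article does not say it outright.

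**Step 2: is there a separating rule?** No section divides SET delivery from testing, and none says that a participant is tested by the nurse who did not counsel them.

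**Step 3: which assessments are exposed?**
- Visit 1 testing: not exposed, as it precedes randomisation.
- QST at visit 2 and 6 months: exposed.
- CPSP testing at 6 months: possibly exposed; no tester is named.
- Primary outcome: pain rated by the participant each morning over postoperative days 1–7, so not nurse-tested.

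**Step 4: illustration of scale.** Inputs from the article: n = 100 and 1:1 allocation, hence 100 / 2 = 50 per arm. Assumptions, not in the article: no drop-out, each nurse counsels 25 SET participants, and the tester is chosen independently of who counselled.

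- SET participants tested by their own SET nurse: 50 × 1/2 = 25 of 50, or 50%, at each post-randomisation visit.
- For a participant the tester did not counsel: P(CBT-I) = 50 / (50 + 25) = 67%, against 50% with no information.

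More generally, let c be the share of SET participants tested by their own nurse. Among participants not counselled by their tester, P(CBT-I) = 50 / (50 + 50(1 − c)) = 1 / (2 − c).

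| Roster | c | P(CBT-I), not counselled by tester |
|---|---|---|
| Strict cross-assignment, caseloads concealed | 0% | 50% |
| Even caseload, independent tester | 50% | 67% |
| Own nurse always tests | 100% | 100% |

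The roster decides whether blinding is kept or lost, and the article does not fix the roster.

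**The case against.** The best defence is that blinding can hold with the staff named. If each SET participant is tested by the other nurse and the CBT-I participants are shared evenly, each nurse tests 25 SET and 25 CBT-I participants, none of whom that nurse has counselled. The chance of CBT-I for any of them is then 25 / 50 = 50%, provided caseloads are kept apart. The masking section states the intended result, and a condensed article may leave rosters to the full protocol. This stands against any claim that blinding is impossible. It does not remove the conflict, because the article states unqualified blinding alongside a staffing description that, as it reads, does not deliver it.

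QST is also partly standardised: a fixed pressure ramp, a button press by the participant, calibrated pinpricks and an undisclosed time limit for cold immersion. Questionnaires, actigraphy, the digital cognitive battery and laboratory assays depend little on the tester. That limits the reach of the problem to QST and perhaps CPSP testing.

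A reader might infer three further things that the documents do not support.

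- **That the bias would favour CBT-I.** Nothing establishes this. A nurse's allegiance to SET, or rapport that lowers reported pain, could act the other way.
- **That participant masking is contradicted** by the SET topic "Education component week 4: psychological treatments for sleep problems". This is a topic heading and the lesson content is not shown. The masking section promises only that the programme content of the other treatment is withheld, and the heading does not show that it is disclosed.
- **That the primary outcome is compromised.** It is self-rated, and the article does not claim that assessor blinding protects a self-report.

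**Conclusion.** The concern holds in a limited form. As written, the two nurses who support SET participants appear to be the two who test, and nothing bars a nurse from testing a participant he or she has counselled. The unqualified blinding claims in Blinding (masking) and in the strengths list are therefore not secured for nurse-administered testing after randomisation.

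Under the assumed even caseload and independent tester, about half of SET participants would be tested by their own SET nurse. The possible range is 0% to 100%. The conclusion rests on the inference that the nurses are the same people and on the absence of any separating rule; the 50% and 67% figures rest on an assumed roster. It would be too strong to say that blinding cannot hold or is absent: cross-assignment would largely preserve it, and even the illustrative roster gives only partial unmasking.

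**What to change.** State in the protocol that no nurse performs post-randomisation testing on a participant he or she has counselled. Either of two arrangements works within the existing staff:

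1. **Cross-assignment.** Both nurses deliver SET, each tests only participants the other counselled or CBT-I participants, and caseloads and session records are concealed from the tester.
2. **Split roles.** One nurse delivers SET and the other does all post-randomisation testing without access to allocation or session records.

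Cross-assignment avoids tying the whole control arm to one provider; split roles are simpler to police. Under either, record the tester's identity at each visit, name who performs CPSP testing and who gives the SET booster, and word the blinding claims in Blinding (masking) and the strengths list to match what then holds.

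The cost is rostering effort, a few sentences of protocol text and less cover when a nurse is absent. No extra staff are needed.

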
#### Testing of neurocognitive function

Different aspects of neurocognitive function will be assessed through a comprehensive digital test battery (Mindmore application, Stockholm, Sweden)^53 54^ including:

Rey auditory learning test—captures the ability to encode, store and recover verbal information.Trail-making test—assesses attention and processing speedCorsi block-tapping test—assesses visuospatial short-term and working memoryStroop colour and word test—assesses the ability to inhibit cognitive interferenceSymbol digit processing test—assesses information processing speedPaced auditory serial addition test—examines attention and working memory.

#### Assessment of blood biomarkers

Blood samples (approximately 24 mL per participant) will be collected by venipuncture. To characterise changes in markers which are relevant to pathways involved in pain and sleep processes, several analyses are planned, including assessment of inflammatory mediators (eg, via Olink proximity extension assay technology), coagulation, monoamine metabolites (through high-performance liquid chromatography), large-scale proteomic analyses, as well as assessment of relevant lipids, metabolites and small molecules (via mass spectrometry).

### Other prespecified outcome measures

#### International Physical Activity Questionnaire short form

The International Physical Activity Questionnaire short form will be used to assess subjective activity level.^55^ Separate scores are generated for walking, moderate-intensity and vigorous-intensity activities. Both categorical (inactive, minimally active, health-enhancing physical activity active) and continuous (median metabolic equivalent of task (MET)-minutes per week; MET=multiple of the resting metabolic rate) measures of physical activity can be calculated. Kilocalories can be computed from MET-minutes.

